## Abstract

**Introduction:**

Critical congenital heart disease (CHD) is associated with neurodevelopmental disorders, recognised as the most common long-term morbidity in affected children. In critical CHD, that is, CHD requiring cardiac surgery within the first 3 months of life, 30%–50% of children have lower developmental scores. Therefore, early identification of at-risk infants is crucial, yet there is no scientifically evaluated care programme in France. This study aims to evaluate early neurodevelopmental status in infants with prenatally diagnosed critical CHD and to determine how intrinsic susceptibility, prenatal and postnatal factors are functionally associated with developmental delay in this population.

**Methods and analysis:**

Caractérisation et Accompagnement des Troubles du neurodéveloppement Associés aux MAlfoRmations cArdiaques coNgénitales (CATAMARAN) is a prospective, multicentre cohort study including 150 fetuses with critical CHD and their parents across eight French tertiary CHD centres. The primary objective will be to estimate the proportion of developmental delay at 6 months using the Bayley Scales of Infant and Toddler Development. Secondary objectives will include exploring potential prenatal, perinatal, perioperative determinants of developmental delay. Data collection will span pregnancy to 6 months of age including clinical assessments, maternal questionnaires (stress and nutrition), multimodal imaging and extensive biobanking (placenta, cord and peripheral blood, stool samples). To explore potential genetic and other multi-omic factors involved in the occurrence of a developmental delay, a case-control analysis will be conducted within the cohort.

**Ethics and dissemination:**

Clinical and biological data will be collected through a secure system, with anonymised samples analysed in specialised facilities under collaborative agreements. Data confidentiality, traceability and long-term storage are ensured through controlled access and audit trails. Study results will be published and shared with families and the public through the patient association Petit Coeur de Beurre. This study received approval from a French ethics committee in November 2024 (no. 2024-A00425-42).

**Trial registration number:**

NCT06690151.

STRENGTHS AND LIMITATIONS OF THIS STUDYThe CATAMARAN study uses a prospective, multicentre, cohort design with embedded case-control multi-omics analyses, enrolling 150 family trios across eight French tertiary congenital heart disease (CHD) centres.The primary neurodevelopmental outcome is assessed using the Bayley Scales of Infant and Toddler Development, Fourth Edition, a norm-referenced, standardised, age-corrected tool validated in CHD and preterm populations.The biobanking protocol integrates six complementary biological matrices (maternal blood, placental tissue, umbilical cord blood, neonatal blood, paternal blood and stool) collected under standardised, accredited conditions (NF S96-900, ISO 9001).Because neurodevelopmental assessments at 6 months have inherent sensitivity limitations, participants will be followed longitudinally up to 24 months of age.The single-country (French) design and exploratory nature of multi-omics analyses limit the immediate generalisability of findings and will require replication in independent international cohorts.

## Introduction

 Congenital heart disease (CHD) is a critical healthcare issue, comprising a group of rare diseases (prevalence <1/2000 live births) that, collectively, are the primary cause of congenital defects, with a birth prevalence of 1%.^1^ Whereas only a minority of patients survived 50 years ago, currently >90% of patients reach adulthood following advances in prenatal diagnosis, surgical techniques and perioperative care.^2^ Therefore, CHD research needs to shift from improving mortality to decreasing morbidity. Neurodevelopmental disorders (NDD) have been recently recognised as the most common morbidity and long-term sequelae in patients with CHD across the lifespan.^3^ The prevalence and severity of NDD increase with the complexity of CHD. In critical CHD, that is, CHD requiring cardiac surgery within the first 3 months of life, 30%–50% of children have lower scores for cognition, language, attention, executive functions, as compared with their peers, with a long-lasting impact on academic achievement, transition to independence and quality of life.^4
5^ Early identification of at-risk infants is primordial as they would benefit the most from early preventive measures. However, while both the American Heart Association and the Association for European Paediatric and Congenital Cardiology have published clinical guidelines regarding the neurodevelopmental risk assessment in grown-up children which operated CHD,^4
6
7^ there is no funded, coordinated, durable and scientifically evaluated multicentric care programme focusing on CHD-associated NDD in France.^8^

Moreover, causes of CHD-associated NDD are mostly unexplained. Early assumptions that NDD were only due to perinatal neurological compromise or perioperative brain injury are now proved to be incorrect. Indeed, despite being multiple, synergistic and cumulative, postnatal risk factors account for <30% of cases, leaving NDD underexplained in over 70%—suggesting that CHD-associated NDD may be preprogrammed.^4
7^ This major breakthrough suggests that as-yet unidentified intrinsic and/or prenatal factors could play a key role. It opens new perspectives in translational research to solve those clinical issues. Among the various causes, genetic factors are a potential major contributor to brain dysmaturation in CHD and shared genetic pathways may alter both heart and brain development.^6
9
10^ Placental abnormalities may also impact brain development, and CHD-associated NDD could partly arise from a triangular interplay between the placenta, the fetal heart and the brain. It is consistent with the Developmental Origins of Health and Disease hypothesis, that is, the in utero programming of early and later-in-life non-communicable cardiometabolic and mental diseases.^7^

Therefore, the *CATAMARAN neonatal* study, which is a prospective cohort study with a case-control multi-omics analysis, aims to comprehensively assess the neurodevelopmental risk at 6 months of age in infants with critical CHD, and to determine how intrinsic susceptibility (ie, genomic variations), prenatal (ie, maternal fetal environment and placental dysregulation) and postnatal (ie, adaptation to extrauterine life and perioperative events) factors are functionally associated with developmental delay in this population.

## Methods

### Study objectives

The primary objective of the *CATAMARAN neonatal* study is to assess the prevalence of developmental delay at 6 months of age in infants with prenatally diagnosed critical CHD.

The secondary objectives are to identify intrinsic, prenatal, perinatal and perioperative determinants of CHD-associated developmental delay.

### General study design and settings

The *CATAMARAN neonatal* study is a multicentre, prospective cohort study involving critical CHD neonates and their two parents with a follow-up duration of 6 months and an expected recruitment time period of 24 months. Recruitment commenced in January 2026, with a planned end of recruitment in December 2027. The primary neurodevelopmental assessments (Bayley Scales of Infant and Toddler Development, Fourth Edition (BSID-IV) at 6 months) will therefore be completed by June 2028.

This is a clinical research study including a cohort and a biocollection, with minimal risk and constraint. It will be conducted in eight French tertiary surgical CHD centres: (1) CHU de Nantes (coordinating centre); (2) Hôpital Necker-Enfants Malades, Paris; (3) CHU de Bordeaux; (4) CHU de Marseille; (5) CHU de Toulouse; (6) CHU de Tours; (7) Hôpital Marie Lannelongue, Le Plessis-Robinson; (8) Hôpital Antoine Béclère, Clamart.

Data will be collected by a co-investigator and a clinical research coordinator at each centre. Patient data will be anonymised and assigned a unique subject number before being transmitted to the principal investigator and clinical research coordinator.

### Study population: patients with critical CHD

The *CATAMARAN neonatal* project will include 150 foetuses with a prenatal diagnosis of sporadic critical CHD and their two blood-related parents when applicable. Prior to any study procedure, written informed consent will be obtained from both parents, for themselves and on behalf of their expected child, following provision of clear and accurate verbal and written information by the attending physician. Consent forms comply with the requirements of the approving ethics committee (Comité de Protection des Personnes, no. 2024-A00425-42).

A CHD will be defined and classified according to the 2021 International Paediatric and Congenital Cardiac Code and the 11th revision of the International Classification of Diseases.^11^ Neonatal CHD surgery risk stratification will be determined by the Risk Stratification for Congenital Heart Surgery (RACHS-2) score.^12^ Cardiac anatomy will be determined based on fetal echocardiogram. The critical character of the CHD will be discussed and validated before inclusion during a team discussion involving a fetal cardiologist, a cardio-paediatrician and a cardiac surgeon.

CHD fetuses will not be included if they exhibit any of the following conditions: suspicion metabolic, genetic or syndromic disease known to be associated with NDD; suspected congenital infection; assisted reproductive technology with third-party reproduction (ie, donor gamete); parents considering pregnancy termination. No restriction on gestational age at delivery is applied: both term (≥37 weeks) and preterm neonates are eligible. Preterm delivery complicates approximately 15%–20% of critical CHD pregnancies and its exclusion would compromise external validity. Gestational age at delivery will be recorded prospectively and included as a covariate in all multivariate models; BSID-IV scores will be interpreted using age-corrected norms for infants born before 37 weeks. A sensitivity analysis restricted to term-born neonates is preplanned.

### Outcome measures

#### Primary outcome

The primary outcome is the proportion of infants with developmental delay at 6 months of age using the BSID-IV.^13^ The ‘Bayley Scales’ is a norm-referenced standardised tool, translated in French and that has been used in clinical practice and in large cohorts to assess developmental functioning in infants and young children aged 16 days to 42 months.^14
15^ It evaluates three key domains: cognitive (sensorimotor development, exploration and manipulation of objects, concept formation, memory), language (receptive and expressive communication) and motricity (fine and gross motricity). Each domain yields standardised scores (mean 100, SD 15), enabling comparison with normative data.

This comprehensive assessment of the development will be performed by a qualified child neuropsychologist using BSID-IV, blinded to the diagnoses, neuroimaging and clinical status of the child. A significant developmental delay will be diagnosed when a child scores at least 1.5 SD below the normative mean in one or more assessed domains.

10^ CATAMARAN will generate one of the largest CHD-NDD trio-WGS datasets to date in France.Phase II—SECONDARY genetic objective, federated network design—NOT a within-study power claim: common variant discovery (genome-wide association study; polygenic score analyses) requires sample sizes of several thousand, far beyond any single critical CHD cohort. The CATAMARAN biocollection is designed as a founding node of a federated national and international genomics network: once recruitment is complete, data will be pooled with other CHD-NDD biobanks in the collaborative network and from the European Reference Network for Rare and Low Prevalence Complex Diseases of the Heart (ERN GUARD-HEART), consistent with the strategy of the Paediatric Cardiac Genomics Consortium. This is a long-term secondary objective, independent of the primary and multi-omics aims of the current study, and no within-study power claim is made.

Outcomes related to acquired predisposing or protective factors for the neurodevelopmental risk are as follows:

19^ Maternal dietary lipid intake (FFQ-ELFE), collected at the same time point as maternal blood sampling, will enable modelling of the dietary contribution to the lipidomic triad. All lipidomic analyses will be performed on the M-Shark mass spectrometry platform (INRAE UMR 1280 PhAN, Nantes).Determine stool metagenomic signatures of developmental delay associated with critical CHD.Assess acquired brain injury and postnatal exposures relevant to developmental delay. A brain MRI will be performed if clinically indicated in the month after the surgery. It will be performed without anaesthesia, using a standardised protocol and the potential lesions will be described using the validated MRI Abnormality Scoring System.^20^

### Intervention timing and data collection

Family trios will undergo a standardised research protocol with clinical, imaging and biological data to be collected at multiple time points (table 1 and figure 1).

**Figure 1 F1:**
[figure not shown]
Study intervention. BSID-IV, Bayley Scales of Infant and Toddler Development, Fourth Edition; CHD, congenital heart disease; ELFE, Étude Longitudinale Française depuis l’Enfance; IES-R, impact of event scale-revised; Q, questionnaire.

**Table 1 T1:** Data recorded and samples collected

Prenatal period	Current healthcare	Biomedical research
Complete fetal ultrasound (T2)	x	
Fetal functional echocardiography (T2 and T3)	x	
Fetal brain MRI (T3) according to clinical indication		x
Biobanking of blood samples of both parents		x
IES-R questionnaire		x
At birth		
Record of pregnancy history	x	
Postnatal transthoracic echocardiogram	x	
Record of in utero exposures, socio-demographics, ELFE questionnaire		x
IES-R questionnaire		x
Placental gross and histopathological examination		x
Biobanking of maternal blood sample, placenta biopsies, umbilical cord blood sample and newborn’s meconium		x
In-hospital perioperative course		
Record of surgical and ICU course data	x	
12-Lead ECG (baseline and postoperative day 2)	x	
Serial transthoracic echocardiograms	x	
Perioperative neuromonitoring (brain haemodynamics)		x
Postoperative brain MRI according to clinical indication (within 10 days)		x
IES-R questionnaire		x
Biobanking of preoperative and postoperative blood samples (neurobiomarkers)		x
Follow-up		
Serial cardiovascular and neurological clinical examinations	x	
Serial transthoracic echocardiograms	x	
Early neurodevelopmental assessment with Amiel-Tison scale (M3)	x	
Biobanking of stools (M1)		x
IES-R questionnaire (M6)		x
Early neurodevelopmental assessment with BSID-IV (M6)		x

BSID-IV, Bayley Scales of Infant and Toddler Development, Fourth Edition; ELFE, Étude Longitudinale Française depuis l’Enfance; ICU, intensive care unit; IES-R, impact of event scale-revised.

#### Clinical data

Eligible fetuses are identified at the routine mid-trimester morphological ultrasound (18–22 weeks) or a subsequent fetal echocardiogram, with diagnosis confirmed by multidisciplinary team consultation typically at 24–28 weeks of gestation. Maternal inclusion and written informed consent occur at 28–35 weeks of gestation, enabling prenatal sampling close to delivery. Paternal and neonatal inclusion occurs at birth. Follow-up data will be recorded prospectively during pregnancy, at birth, at the surgery, at 3 and 6 months of age. Data on environmental stress exposures (maternal infection, inflammation, smoking, alcohol, substance abuse, medical treatment during the pregnancy) will be collected from the maternal electronic health records. After delivery, anthropometric measurements of mothers and babies, gestational age, prenatal and intrapartum complications (pre-eclampsia, gestational diabetes, fetal growth restriction) and newborn adaptation to extrauterine life parameters will be assessed. The following perioperative variables will be systematically recorded: (i) surgical: CPB duration, aortic cross-clamp time, circulatory arrest duration and temperature, selective cerebral perfusion use, haematocrit and minimum temperature on CPB, transfusion volumes, RACHS-2 score; (ii) ICU/postoperative: duration of mechanical ventilation and inotropic support, lowest mean arterial pressure and peripheral oxygen saturation in the first 48 hours, occurrence of low cardiac output syndrome (need for extracorporeal membrane oxygenation or ≥3 inotropes for >48 hours), acute kidney injury (Kidney Disease: Improving Global Outcomes criteria), seizures, ICU days, total hospital stay; (iii) neurological monitoring: continuous perioperative cerebral near-infrared spectroscopy (regional oxygen saturation, desaturation burden <50%); postoperative brain MRI scored with the MRI Abnormality Scoring System^20^; (iv) neurobiomarkers: plasma neurofilament light chain and glial fibrillar acidic protein on days 0, 1 and 2 postsurgery. Patients will undergo prospective cardiovascular follow-up including serial echocardiograms as per routine practice.

#### Biobanking

Before birth, a mother’s blood sample will be taken. At birth, placenta will be sampled, snap frozen in dry ice and stored at −80°C. At the same time, venous cord blood samples will be collected. Proband’s blood samples will be taken at the time of surgery along with a blood sample from the father for the genetic study (preoperative day 0) and postoperatively (day 1 and day 2) for the postnatal exposure (neurobiomarkers). All these blood samples will be processed within 1 hour and stored at −80°C. Finally, a collection of stools will be realised at birth and at 1 month of age.

All human biological samples (placenta, blood and stools) will be stored in the Biobanking Core Facility at Nantes University Hospital (NF S96-900 and ISO 9001 accreditations), in the existing paediatric biocollection supervised by the study coordinator.

### Statistical analyses

#### Sample size justification

According to the study by Gunn *et al* using the same screening tool in its previous version (Bayley-III), a developmental delay was detected in 32% of patients at the age of 2 years.^21
22^ In our selected population, we expect this rate to be at least as high. To ensure adequate precision of the estimated proportion, we considered a range of possible rates from 5% to 35%. Assuming a 5% loss to follow-up, a total sample size of 150 patients will allow estimation of the proportion of infants with a developmental delay with 95% CIs ranging from 7% to 16% (exact Clopper-Pearson method), depending on the true underlying rate.

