#### Statistical analyses

All variables will be described overall and by relevant subgroup. The description will include counts and percentages for qualitative variables and minimum, maximum, mean, SD and median for quantitative variables. The proportion of infants with developmental delay at 6 months, defined as a BSID-IV score ≥1.5 SD below the normative mean in at least one of the measured domains, will be calculated, with 95% CIs estimated using the exact Clopper-Pearson method. To identify factors associated with developmental delay (clinical perinatal, neonatal and postnatal conditions), bivariate analyses will be performed, followed by multivariate logistic regression models adjusting for potential confounders. To explore potential genetic, transcriptomic and other multi-omic factors involved in the occurrence of a developmental delay, a case-control analysis will be conducted within the cohort. Cases will include infants who meet the criteria for developmental delay at 6 months, while controls will be those who do not. Multivariate models will then be applied to account for additional individual risk factors. All tests will be two-sided and the significance threshold will be set at 5%. For multi-omics discovery analyses, a false discovery rate correction (Benjamini-Hochberg method) will be applied independently for each omic stratum. All multi-omics findings will be explicitly reported as hypothesis-generating, pending replication in independent cohorts. Missing data for continuous covariates will be handled by multiple imputation (five imputed datasets, fully conditional specification). A preplanned sensitivity analysis restricted to term-born neonates (≥37 weeks) will assess robustness of the primary endpoint.

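### Minor: the stated precision of 7% to 16% should read about 8 to 16 points of full interval width, and it stops at a 35% rate although a rate of at least 32% is expected

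*Protocol article*

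**What the plan says.** In the protocol article, under Sample size justification, an earlier study with the previous version of the Bayley scales found delay in 32% of patients at 2 years. The authors then write "In our selected population, we expect this rate to be at least as high". For the precision calculation, "we considered a range of possible rates from 5% to 35" per cent.

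The inputs are 150 enrolled infants and a 5% loss to follow-up. The precision that this is said to give is "95% CIs ranging from 7% to 16% (exact Clopper-Pearson method), depending on the true underlying rate". No power calculation is given for the primary objective; this precision statement is the only quantitative support for 150.

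The Statistical analyses section commits the primary estimate to the same interval, "with 95% CIs estimated using the exact Clopper-Pearson method". The Introduction reports that in critical congenital heart disease "30%–50% of children have lower scores for cognition, language, attention, executive functions" compared with peers.

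**The concern.** Three things in the sentence do not fit together.

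- **What the figures are.** They are introduced as confidence intervals running from one percentage to another, which at first reads like interval limits. Only a full width (upper minus lower limit) is compatible with rates of 5% to 35%.
- **The lower figure.** A width of 7 points at a 5% rate looks too small for an exact interval with about 142 infants.
- **The range of rates.** The expectation is 32% or more, with no upper bound. Most of the 5% to 35% range therefore lies below the expected rate, and everything above 35%, where intervals are widest, is left out. A reader may take 16 points as the worst case, or hope for something nearer 7.

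What is at stake is the accuracy of the precision claim for the primary outcome, not the conduct of the study.

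**Working it through.** **Inputs**

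- Enrolled: 150; loss 5% (Sample size justification). Assessed: 150 × 0.95 = 142.5, so 142 or 143.
- Interval: two-sided 95% exact Clopper-Pearson (Sample size justification and Statistical analyses).
- Rates: 5% to 35% as planned; 32% as the reference rate; 40% and 50% added here, because the expectation is open above 32%.

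**Formula**

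For x events among n infants:

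- lower limit = 0.025 quantile of Beta(x, n − x + 1)
- upper limit = 0.975 quantile of Beta(x + 1, n − x)
- full width = upper − lower

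**Step 1: the plan's own figures**

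| Rate | n | x | 95% limits | Full width (points) | Plan states |
|---|---|---|---|---|---|
| 5% | 142 | 7 | 2.0% to 9.9% | 7.9 | 7 |
| 5% | 143 | 7 | 2.0% to 9.8% | 7.8 | 7 |
| 35% | 142 | 50 | 27.4% to 43.7% | 16.3 | 16 |
| 35% | 143 | 50 | 27.2% to 43.4% | 16.2 | 16 |

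The upper end reproduces. The lower end rounds to 8. Taking 8 events instead of 7 makes it wider still (8.3 points at either n). A width of 7.0 points at a 5% rate would need about 179 assessed infants.

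**Step 2: could another route give 7 and 16?**

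- Exact, loss ignored, events rounded down: 7/150 gives 7.48 and 52/150 gives 15.8. These round to 7 and 16, but the stated loss is not applied.
- Exact, loss applied, decimals cut off instead of rounded: 7.8 or 7.9 becomes 7, and 16.2 or 16.3 becomes 16.
- Wald, n = 142, width = 2 × 1.96 × √[p(1 − p)/n]. At 5%: 2 × 1.96 × √(0.05 × 0.95/142) = 7.2 points. At 35%: 2 × 1.96 × √(0.35 × 0.65/142) = 15.7 points. These also round to 7 and 16.

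Several routes give the printed pair, so the document does not show which was used. None is the stated method, with the stated loss, conventionally rounded.

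**Step 3: the expected region (exact, n = 142)**

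| Rate | x | Full width (points) |
|---|---|---|
| 15% | 21 | 12.3 |
| 32% | 45 | 15.9 |
| 35% | 50 | 16.3 |
| 40% | 57 | 16.7 |
| 50% | 71 | 17.0 |

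The width peaks at 50%, so 17.0 is the worst case. Against the stated maximum of 16 the shortfall is 17.0 − 16 = 1.0 point. At the lower end it is 7.9 − 7 = 0.9 point at most.

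**The case against.** The strongest defence is that the figure that matters is right. At 32% to 35% the exact width is about 16 points, as stated, and the error sits at a 5% rate that the study does not expect. That stands, and it is why the point is minor.

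It can also be said that width is the only coherent reading, so the missing word misleads nobody for long. That largely stands; naming the quantity is a matter of clarity.

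Four stronger readings are tempting and should not be drawn:

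- **That the Wald formula was used.** The Wald pair does round to 7 and 16, but so do the exact values when truncated. The document cannot separate the two.
- **That the expected region is not covered.** The range includes 32% to 35%. Only rates above 35% are missing.
- **That the Introduction shows the study expects 40% to 50%.** Its 30% to 50% describes lower scores than peers, including attention and executive functions. It is not the primary outcome, a Bayley score at least 1.5 SD below the norm at 6 months. It is indirect support at best; the sample size section's own expectation carries the point.
- **That a 5% rate is impossible because delay counts "in one or more assessed domains".** How often such a rule flags children in the normative population depends on correlations between domains, which the document does not give. Considering low rates is a planning choice, not an arithmetic error, and no additional normative analysis is called for here.

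**Conclusion.** The point holds as a minor reporting error. Under the stated inputs the lower precision figure should be about 8 points rather than 7; the upper figure of 16 is correct for rates of 32% to 35%. Because the range ends at 35%, the stated maximum is about 1 point below the true maximum of 17.0 at a 50% rate. For rates from 32% to 50% the width to expect is about 16 to 17 points.

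A reader might infer that 150 infants are too few or that precision is seriously overstated. Neither follows: each discrepancy is about 1 point or less, and the design, the sample size and the planned interval method are unaffected.

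This rests on reading the figures as full widths, on 142 or 143 assessed infants, and on event counts rounded to whole infants.

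**What to change.** Replace the precision sentence with, for example: with about 142 assessed infants (150 enrolled, 5% lost), the full width of the exact Clopper-Pearson 95% confidence interval is about 8 points at a rate of 5%, 12 at 15%, 16 at 32% to 35%, and 17 at 50%. Change the stated planning range so that it extends above 35%, in line with the expectation of at least 32%.

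The cost is one or two sentences. There are no additional infants and no change to the analysis; the stated precision becomes about 1 point less favourable at each end.
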